## **11 ENDPOINTS**

### **11.1 Safety**

The safety of immunization with the seven DNA plasmids carrying HIV-1 genes and the MVA will be assessed by clinical features as well as standard biochemical and hematological laboratory tests. Any worsening of the severity grade will be considered for causality with the vaccine.

Safety endpoints: Adverse events will be assessed using a standard format for soliciting local and systemic reactogenicity to the vaccine and collection of unsolicited adverse events. Solicited reactogenicity will be evaluated for 7 days following each vaccination. All other AE will be collected from the time of first injection until 3 months after the last injection.

The primary safety parameters will be graded according to the DAIDS Table for Clinical and Lab Criteria for Definitions (*see Appendix 9*) and are:

1. Local adverse event Grade 3 or above (pain, cutaneous reactions including indurations)
2. Systemic adverse event Grade 3 or above (fever, chills, headache, nausea, malaise, myalgia, and arthralgia)

3. Other clinical and laboratory adverse event Grade 3 or above confirmed at examination or on repeat testing respectively

The relationship to the vaccine should be evaluated as:

- 1= not related
- 2= probably not related
- 3= possibly related
- 4= probably related
- 5= definitely related

Tests for possible toxicity due to vaccination will include: Liver function tests, renal function tests and complete blood count and differential with platelets. Any event attributable to vaccine leading to discontinuation of the immunization regimen must be documented.

Data on local and systemic events listed above will be solicited with specific questions or using a diary card for a minimum of 7 days following each immunization. Data on other clinical events and laboratory events will be collected with an open question at each visit and through routine scheduled investigations respectively.

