## 12 SAFETY AND IMMUNOGENICITY ASSESSMENTS

### 12.1 Safety assessment

Local and systemic assessments whether normal or abnormal will be recorded starting from 30 minutes up to 4 weeks after immunization in the following intervals: 30 minutes as direct observation after immunization, at the evening of the vaccination day and at days 1-7 as recorded by diary cards by the participants with clinic or home visit if indicated, plus follow-up safety visits 2 weeks and 4 weeks after each immunization. While study personnel will use the vaccine/reaction form (**CRF 10-I**) to record all local and systemic events at the clinic, participants will use diary cards at home for the same. On the Adverse Events Form (**CRF 6-I**) all medical events throughout the entire study period will be reported, excluding those local or systemic reactions indicated on the Vaccine/Reaction Form (**CRF 10-I**) during the first 7 days post vaccination. The study site will contact participants at the first day after vaccination for an adverse events/reaction interview. Participants will be instructed to call or report to the specified study personnel immediately if any unusual or severe sign or symptom appears after immunization. Participants with suspected grade 3 or above events should be seen in the clinic at the time of maximal symptoms, if possible, and will be followed up clinically until resolution of symptoms.

An adverse event is any undesired, noxious or pathological change in a participant as indicated by physical signs, symptoms, and/or laboratory changes that occurs following administration of one of the vaccines, whether or not considered vaccine related. This definition includes intercurrent illnesses or injuries, and exacerbation of pre-existing conditions.

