#### **12.1.1 Local adverse events**

Pain at the injection site will be graded by the volunteer according to the criteria in the DAIDS Table for Clinical and Lab Criteria for Definitions (**see Appendix 9**) as mild (1) moderate (2), severe (3) or serious/life threatening (4) and recorded in the appropriate case record form. In the diary card grading will refer only to mild (1) moderate (2) and severe (3) as the distinction between severe and serious should be made in association with the medical officer after having reported to the clinic once the volunteer has left clinic. Swelling, redness and indurations will be recorded as the maximum diameter as well as the presence of any itching or other discomfort and any medication taken for relief of symptoms. Blistering (vesiculation) or ulceration will be graded according to size, depth, time to healing and character of blisters (blood-filled).

Clinical staff will complete the case record form following each immunization. In the event that there are two observations on the same day, those confirmed at a visit will take precedence over diary card observations in the analysis. Study personnel should verify all grade 3 or 4 events.

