## Evening of Vaccination

Date: \_\_\_\_\_

Temp: \_\_\_\_\_ Time Taken: \_\_\_\_\_

If you have a fever and wish to take your temperature during the night, record your additional temperature:

Temp: \_\_\_\_\_ Time Taken: \_\_\_\_\_ Temp: \_\_\_\_\_ Time Taken: \_\_\_\_\_

Are you taking any medication? Yes No

Specify: \_\_\_\_\_

Please use the symptom scale at the bottom of the page

| General Symptoms | None | Mild | Moderate | Severe |
|------------------|------|------|----------|--------|
| Malaise/ Fatigue |      |      |          |        |
| Chills           |      |      |          |        |
| Aching Joints    |      |      |          |        |
| Muscle Aches     |      |      |          |        |
| Headache         |      |      |          |        |
| Nausea           |      |      |          |        |
| Vomiting         |      |      |          |        |

| Injection Site Symptoms | None                   | Mild | Moderate | Severe | None                   | Mild | Moderate | Severe |
|-------------------------|------------------------|------|----------|--------|------------------------|------|----------|--------|
| Local Pain              |                        |      |          |        |                        |      |          |        |
| Local Itching           |                        |      |          |        |                        |      |          |        |
| Warmth                  |                        |      |          |        |                        |      |          |        |
| Swelling (in cm)        | ____. __X _____. __ cm |      |          |        | ____. __X _____. __ cm |      |          |        |
| Redness (in cm)         | ____. __X _____. __ cm |      |          |        | ____. __X _____. __ cm |      |          |        |
| Induration (in cm)      | ____. __X _____. __ cm |      |          |        | ____. __X _____. __ cm |      |          |        |
| Clear blister (in cm)   | ____. __X _____. __ cm |      |          |        | ____. __X _____. __ cm |      |          |        |
| Blood blister (in cm)   | ____. __X _____. __ cm |      |          |        | ____. __X _____. __ cm |      |          |        |
| Papule (in cm)          | ____. __X _____. __ cm |      |          |        | ____. __X _____. __ cm |      |          |        |

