| Tafadhali rekodi vipimo kwa sm, urefu na upana mkubwa zaidi ( Mfano: 01.5 X 02.5 sm )                                                                                                                                                                                                                                                                                                                                                                                                                                                                                                                                                                                                                                                                                                                                                                                                                                                                                                                                                                                                                                                                                                                                                                                                                                                                                                                                                                                                                                                                                                                                                                                                                                                                                                                                                                                                                                                                                                                                                                                                                                                                                                                                                                                                                                                                                                                                                                                                                            |                             |        |         |      |                             |                |         |      |  |                  |  |  |  |                           |        |        |         |      |        |        |         |      |                               |  |  |  |  |  |  |  |  |                             |  |  |  |  |  |  |  |  |                              |  |  |  |  |  |  |  |  |                                  |                             |  |  |  |                             |  |  |  |                             |                             |  |  |  |                             |  |  |  |                          |                             |  |  |  |                             |  |  |  |                                      |                             |  |  |  |                             |  |  |  |                                  |                             |  |  |  |                             |  |  |  |                 |                             |  |  |  |                             |  |  |  |

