| Injection site pain (pain without touching)
Or
Tenderness (pain when area is touched) | Pain/tenderness causing no or minimal limitation of use of limb                                                                                    | Pain/tenderness limiting use of limb OR Pain/tenderness causing greater than minimal interference with usual social & functional activities | Pain/tenderness causing inability to perform usual social & functional activities                                                                                                                       | Pain/tenderness causing inability to perform basic self-care function OR Hospitalization (other than emergency room visit) indicated for management of pain/tenderness |
| Injection site reaction (localized)                                                         |                                                                                                                                                    |                                                                                                                                             |                                                                                                                                                                                                         |                                                                                                                                                                        |
| Adult > 15 years                                                                  | Erythema OR Induration of 5x5 cm – 9x9 cm (or 25 cm  – 81cm  )                                                             | Erythema OR Induration OR Edema > 9 cm any diameter (or > 81 cm  )                                                              | Ulceration OR Secondary infection OR Phlebitis OR Sterile abscess OR Drainage                                                                                                                           | Necrosis (involving dermis and deeper tissue)                                                                                                                          |

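### Section 12.1.1 records redness and induration as one maximum diameter, which cannot decide between ungraded and Grade 1 under Appendix 9; the diary cards already ask for two dimensions

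*Protocol*

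**What the plan says.** Three parts of the protocol deal with the size of a local reaction.

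- **Diary cards (Appendix 8A and 8B).** Each measured sign has two blanks joined by an X, for each arm. In the English card the first such row begins "Swelling (in cm". The Swahili card adds an instruction on each daily page, "Tafadhali rekodi vipimo kwa sm, urefu na upana mkubwa zaidi", which asks for the greatest length and width in cm and gives 1.5 x 2.5 as its example. The English card has the fields but no measuring instruction.
- **Section 12.1.1.** "Swelling, redness and indurations will be recorded as the maximum diameter". The same section says that when there are two observations on one day, the one confirmed at a visit is used in the analysis in preference to the diary.
- **Appendix 9, adult injection site reaction.** Grade 1 is "Erythema OR Induration of 5x5 cm – 9x9 cm", or 25 to 81 cm². Grade 2 is "Erythema OR Induration OR Edema > 9 cm any diameter", or more than 81 cm². Grade 3 has no size criterion: "Ulceration OR Secondary infection OR Phlebitis OR Sterile abscess OR Drainage".

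Sections 8.4 and 9.3 have diary entries transcribed to CRF 10-I after review with the volunteer. Section 12.1 has staff use the same form for what they see at the clinic. Section 20.1 evaluates two against five intradermal injections on local events, including induration. Section 20.4 summarises events by severity and counts each subject once. The primary local safety parameter in Section 11.1 is "Local adverse event Grade 3 or above (pain, cutaneous reactions including indurations").

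**The concern.** The diary and the grading table both use two dimensions, while the text that tells staff what to record asks for one. Staff who follow 12.1.1 literally write a number from which Grade 1 cannot be determined, and on days with two observations that number replaces the volunteer's two-dimensional entry in the analysis. A width that was never measured cannot be recovered later, so the analysis plan cannot repair this.

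What is at stake is the low end of the severity tables and the low-grade part of the comparison of two with five injections. Graders faced with a single diameter would have to choose their own convention, and the protocol gives them none.

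**Working it through.** **Inputs.** Appendix 9 adult cut-offs: Grade 1 is 5x5 to 9x9 cm, or 25 to 81 cm²; Grade 2 is any diameter above 9 cm, or more than 81 cm². Recording rule in 12.1.1: maximum diameter. Recording on the diary: length x width.

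**Step 1: the table's own figures.** 5 x 5 = 25 cm² and 9 x 9 = 81 cm². The area cut-offs agree with the dimensions.

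**Step 2: what one diameter can decide.** Let d be the longest side and w the width, with w no larger than d. Area = d x w.

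- d below 5 cm: the area is at most d x d, which is below 25 cm². The reaction is ungraded whatever its width.
- d above 9 cm: Grade 2 whatever the width, by the any-diameter criterion.
- d from 5 to 9 cm: Grade 1 on area needs w of at least 25/d. For d = 8 this is 25/8 = 3.125 cm; for d = 9 it is 25/9 = 2.78 cm. The diameter alone does not show which side of this the reaction lies.

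**Step 3: examples for redness or induration, reading the Appendix 9 alternatives as joined by *or*.**

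| Length x width (cm) | Area (cm²) | Recorded under 12.1.1 | Grade under Appendix 9 | Does the diameter decide it? |
|---|---|---|---|---|
| 6 x 2 | 12 | 6 cm | ungraded | no |
| 8 x 2 | 16 | 8 cm | ungraded | no |
| 8 x 3 | 24 | 8 cm | ungraded | no |
| 8 x 4 | 32 | 8 cm | Grade 1 | no |
| 9 x 2 | 18 | 9 cm | ungraded | no |
| 10 x 2 | 20 | 10 cm | Grade 2 | yes |
| 12 x 7 | 84 | 12 cm | Grade 2 | yes |

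**Step 4: direction if a convention is imposed.** Assume that graders read a single diameter of 5 to 9 cm as Grade 1. This is my assumption; the protocol states no one-dimension cut-off for Grade 1. Over all length x width pairs up to 15 cm in steps of 0.1 cm, the only disagreement with Appendix 9 is then from ungraded to Grade 1. It occurs when the longest side is 5 to 9 cm and the area is below 25 cm². Grade 2 never disagrees, and size never yields Grade 3. The grid shows where disagreement is possible, not how often it would occur; the documents give no distribution of reaction sizes.

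**Step 5: which signs.** Grade 1 names erythema and induration only; edema first appears at Grade 2. Swelling therefore has no size-based Grade 1 to misassign.

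**Step 6: where clinic and diary overlap.** Section 9.3 has a staff observation 30 minutes after injection, diary entries that evening and for 7 days, and scheduled visits at 2 and 4 weeks. The precedence rule therefore applies on the vaccination day and at any extra visit or contact during the diary week. For other diary days the two-dimension entry is the only source.

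**The case against.** The case against is substantial and narrows the point.

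- **Loss of the width.** A reader might infer that the CRF drops it. The documents do not show this. Section 12.1.1 does not say that the maximum diameter is the only number recorded, both cards hold two numbers, these are transcribed to CRF 10-I, and that form is not in the document. It may already have two fields.
- **General over-grading.** A reader might infer that every long, narrow reaction is graded too high. Above 9 cm Appendix 9 itself assigns Grade 2 on one diameter, so nothing changes there. Between 5 and 9 cm, over-grading needs a one-dimension cut-off that the protocol does not contain. What stands is that the grade cannot be determined, not that it is known to be too high.
- **The precedence rule resolves the conflict.** It does say which value is used. But the value it prefers is the one that 12.1.1 describes with a single diameter.
- **Bias between groups.** The same card and rules apply to every group, and no differential error is shown. Group III receives three injections in one arm, so merging of neighbouring reactions can be imagined, but the protocol does not give their spacing.
- **Blank size fields.** These rows have no tick for none, although 12.1 says "Local and systemic assessments whether normal or abnormal will be recorded starting from 30 minutes up to 4 weeks after immunization". A reader might infer that blanks bias rates downwards. Section 8.4 has recording deficiencies discussed with the volunteer when the card is collected, and 20.4 counts each subject once, so one blank field does not remove an affected subject. This is not part of the finding.

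**Conclusion.** The inconsistency is real and minor. As 12.1.1 is worded, a redness or induration whose longest side is 5 to 9 cm cannot be placed as ungraded or Grade 1 from the number it asks staff to record, and such a clinic value outranks a same-day diary entry that could place it. The consequence reaches the low-grade rows of the severity summaries in 20.4 and the comparison of two with five injections in 20.1. Grade 2 and the primary local safety parameter are untouched.

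The conclusion rests on reading Appendix 9 with its size alternatives joined by *or*, and on staff following 12.1.1 as written. How many subjects would be affected cannot be estimated from the documents.

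**What to change.** In 12.1.1, replace the maximum-diameter rule with the recording that the diary already uses: greatest length x width in cm for swelling, redness and induration, at clinic visits as well as at home. Check that CRF 10-I has room for both numbers, and add the second if it does not. Leave the grading to Appendix 9 as it stands, with no new cut-off.

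The cost is one sentence in 12.1.1 and, only if the form lacks it, one extra size field on CRF 10-I.

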**Appendix 9: DAIDS Table for Clinical and Lab Criteria**

| CLINICAL                                                                                                                                                     |                                                                                       |                                                                                                                   |                                                                                                          |                                                                                                                                                                                 |
|---------------------------------------------------------------------------------------------------------------------------------------------------------------------|---------------------------------------------------------------------------------------|-------------------------------------------------------------------------------------------------------------------|----------------------------------------------------------------------------------------------------------|---------------------------------------------------------------------------------------------------------------------------------------------------------------------------------|
| PARAMETER                                                                                                                                                    | GRADE 1
MILD                                                               | GRADE 2
MODERATE                                                                                       | GRADE 3
SEVERE                                                                                | GRADE 4
POTENTIALLY
LIFE-THREATENING                                                                                                                             |
| ESTIMATING SEVERITY GRADE                                                                                                                                    |                                                                                       |                                                                                                                   |                                                                                                          |                                                                                                                                                                                 |
| Clinical adverse event NOT identified elsewhere in this DAIDS AE grading table                                                                                      | Symptoms causing no or minimal interference with usual social & functional activities | Symptoms causing greater than minimal interference with usual social & functional activities                      | Symptoms causing inability to perform usual social & functional activities                               | Symptoms causing inability to perform basic self-care functions OR Medical or operative intervention indicated to prevent permanent impairment, persistent disability, or death |
| SYSTEMIC                                                                                                                                                     |                                                                                       |                                                                                                                   |                                                                                                          |                                                                                                                                                                                 |
| Acute systemic allergic reaction                                                                                                                                    | Localized urticaria (wheals) with no medical intervention indicated                   | Localized urticaria with medical intervention indicated OR Mild angioedema with no medical intervention indicated | Generalized urticaria OR Angioedema with medical intervention indicated OR Symptomatic mild bronchospasm | Acute anaphylaxis OR Life-threatening bronchospasm OR laryngeal edema                                                                                                           |
| Chills                                                                                                                                                              | Symptoms causing no or minimal interference with usual social & functional activities | Symptoms causing greater than minimal interference with usual social & functional activities                      | Symptoms causing inability to perform usual social & functional activities                               | NA                                                                                                                                                                              |
| Fatigue
Malaise                                                                                                                                                  | Symptoms causing no or minimal interference with usual social & functional activities | Symptoms causing greater than minimal interference with usual social & functional activities                      | Symptoms causing inability to perform usual social & functional activities                               | Incapacitating fatigue/ malaise symptoms causing inability to perform basic self-care functions                                                                                 |
| Fever (nonaxillary)                                                                                                                                                 | 37.7 – 38.6°C                                                                         | 38.7 – 39.3°C                                                                                                     | 39.4 – 40.5°C                                                                                            | > 40.5°C                                                                                                                                                                        |
| Pain (indicate body site)
DO NOT use for pain due to injection (See Injection Site Reactions: Injection site pain)
See also Headache, Arthralgia, and Myalgia | Pain causing no or minimal interference with usual social & functional activities     | Pain causing greater than minimal interference with usual social & functional activities                          | Pain causing inability to perform usual social & functional activities                                   | Disabling pain causing inability to perform basic self-care functions OR Hospitalization (other than emergency room visit) indicated                                            |
| Unintentional weight loss                                                                                                                                           | NA                                                                                    | 5 – 9% loss in body weight from baseline                                                                          | 10 – 19% loss in body weight from baseline                                                               | ≥ 20% loss in body weight from baseline OR Aggressive intervention indicated [e.g., tube feeding or total parenteral nutrition (TPN)]                                           |

| CLINICAL                                                                                    |                                                                                                                                                    |                                                                                                                                             |                                                                                                                                                                                                         |                                                                                                                                                                        |
|---------------------------------------------------------------------------------------------|----------------------------------------------------------------------------------------------------------------------------------------------------|---------------------------------------------------------------------------------------------------------------------------------------------|---------------------------------------------------------------------------------------------------------------------------------------------------------------------------------------------------------|------------------------------------------------------------------------------------------------------------------------------------------------------------------------|
| PARAMETER                                                                                   | GRADE 1
MILD                                                                                                                                    | GRADE 2
MODERATE                                                                                                                         | GRADE 3
SEVERE                                                                                                                                                                                       | GRADE 4
POTENTIALLY
LIFE-THREATENING                                                                                                                             |
| INFECTION                                                                            |                                                                                                                                                    |                                                                                                                                             |                                                                                                                                                                                                         |                                                                                                                                                                        |
| Infection (any other than HIV infection)                                                    | Localized, no systemic antimicrobial treatment indicated AND Symptoms causing no or minimal interference with usual social & functional activities | Systemic antimicrobial treatment indicated OR Symptoms causing greater than minimal interference with usual social & functional activities  | Systemic antimicrobial treatment indicated AND Symptoms causing inability to perform usual social & functional activities OR Operative intervention (other than simple incision and drainage) indicated | Life-threatening consequences (e.g., septic shock)                                                                                                                     |
| INJECTION SITE REACTIONS                                                             |                                                                                                                                                    |                                                                                                                                             |                                                                                                                                                                                                         |                                                                                                                                                                        |
| Injection site pain (pain without touching)
Or
Tenderness (pain when area is touched) | Pain/tenderness causing no or minimal limitation of use of limb                                                                                    | Pain/tenderness limiting use of limb OR Pain/tenderness causing greater than minimal interference with usual social & functional activities | Pain/tenderness causing inability to perform usual social & functional activities                                                                                                                       | Pain/tenderness causing inability to perform basic self-care function OR Hospitalization (other than emergency room visit) indicated for management of pain/tenderness |
| Injection site reaction (localized)                                                         |                                                                                                                                                    |                                                                                                                                             |                                                                                                                                                                                                         |                                                                                                                                                                        |
| Adult > 15 years                                                                  | Erythema OR Induration of 5x5 cm – 9x9 cm (or 25 cm  – 81cm  )                                                             | Erythema OR Induration OR Edema > 9 cm any diameter (or > 81 cm  )                                                              | Ulceration OR Secondary infection OR Phlebitis OR Sterile abscess OR Drainage                                                                                                                           | Necrosis (involving dermis and deeper tissue)                                                                                                                          |
| Pediatric ≤ 15 years                                                                 | Erythema OR Induration OR Edema present but ≤ 2.5 cm diameter                                                                                      | Erythema OR Induration OR Edema > 2.5 cm diameter but < 50% surface area of the extremity segment (e.g., upper arm/thigh)                   | Erythema OR Induration OR Edema involving ≥ 50% surface area of the extremity segment (e.g., upper arm/thigh) OR Ulceration OR Secondary infection OR Phlebitis OR Sterile abscess OR Drainage          | Necrosis (involving dermis and deeper tissue)                                                                                                                          |
| Pruritis associated with injection
See also Skin: Pruritis (itching - no skin lesions)   | Itching localized to injection site AND Relieved spontaneously or with < 48 hours treatment                                                        | Itching beyond the injection site but not generalized OR Itching localized to injection site requiring ≥ 48 hours treatment                 | Generalized itching causing inability to perform usual social & functional activities                                                                                                                   | NA                                                                                                                                                                     |
| SKIN – DERMATOLOGICAL                                                                |                                                                                                                                                    |                                                                                                                                             |                                                                                                                                                                                                         |                                                                                                                                                                        |
